### Sample size estimation and selection criteria

2.4

The sample size has been calculated assuming that the prevalence of the variables of interest (e.g. proportion of individuals with poor health-related quality of life, proportion of individuals with limited critical health literacy etc.) does not exceed 30%, with an absolute precision of ± 5% and a confidence level of 95%. A design effect of 1.5 has been applied, following the recommendations of the World Health Organization's (WHO) STEPS guidelines (13) for complex designs. In addition, a rejection rate of up to 20% has been considered, implying the need to recruit at least 590 participants. The proposed inclusion of 600 participants also ensures the estimation of indicators for specific subgroups (such as by sex) with an absolute precision of close to ± 5%.

A before-and-after analysis will be conducted with 600 independent participants at each time point, selected using comparable samples and applying the same inclusion criteria and sampling design. This sample size is sufficient to detect significant differences in both our main outcome (i.e., health-related quality of life) and secondary variables. In the case of health-related quality of life, it allows us to identify absolute changes of around 10%, with a confidence level of 95% and a statistical power close to 80%. The exact power will depend on the initial prevalence of the indicator and the magnitude of the observed effect. Although the analysis of social inequalities may have lower power due to stratification by subgroups, we estimate that the sample size will be sufficient to identify relevant trends and significant differences in social inequalities in the studied sample.

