### Data analysis

2.8

As main outcome, the mean and the standard deviation of the health-related quality of life will be calculated and stratified by sex, age group and other sociodemographic variables, thus allowing for an equity analysis. In addition, we will perform multivariate models to analyse the association of sociodemographic characteristics on health-related quality of life and secondary variables (critical health literacy, social capital, community capital, and knowledge, attitudes and practices on personal antibiotic use). These results will be also crucial to enrich the discussions in the co-creation process, facilitating an equitable and contextualized approach to the identified health issues. A before-and-after analysis will also be carried out using the population-based survey data to assess changes across time points (pre- and post-intervention) in the population in both main and secondary variables, providing evidence on the evolution of health-related quality of life and other relevant social determinants of health. Specifically, firstly, the normal distribution of physical and mental HRQoL will be tested by conducting Shapiro-Wilk tests and plotting histograms. In case of observing a non-normal distribution, these variables will be dichotomised using the median value of the whole sample (pre- and post-intervention). Therefore, given the distribution of health-related quality of life, multivariate linear regression models or Poisson regression models with robust standard errors will be used to estimate absolute and relative changes across time points. Additional models will be run, including interaction terms of time with sex, age group and other sociodemographic variables to assess the changes in social inequalities in HRQoL. Contextual variables will be included, such as economic development, unemployment rate and poverty rate at the regional level of the province of Alicante before and after the intervention, retrieved from the National Institute of Statistics (INE) and the statistics portal of the Valencian Community in Spain. Statistical analysis will be adjusted for sex, age group and other sociodemographic variables such as education, ethnicity, migration status, household income, employment status and marital status, among others. Multiple imputation will be used for missing data on HRQoL and secondary variables. For the remaining covariates, an additional category of missing values will be created to include these individuals in the statistical analyses.

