
For statistical analysis, we will use the latest version of Stata/SE (StataCorp, Texas, USA), and R: A language and environment for statistical computing (R Foundation for Statistical Computing, Vienna, Austria). The *p*-value obtained in the hypothesis tests performed will be described. Although we will use a *p*-value < 0.05 as a reference to identify statistically significant differences, this value should be interpreted with caution when subgroup stratified analyses with smaller sample sizes are conducted. The possibility of a type II error (false acceptance of the null hypothesis) will be considered, allowing for a more nuanced and contextualized interpretation of the results, thus avoiding the premature exclusion of potentially relevant trends in under-represented subgroups. No survey weights will be used in statistical analyses.

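### The sample-size section says 600 per wave suffices for inequality analyses, but this is unsupported for changes in inequality: a 10-point time-by-group interaction has about 23–34% power with the plan's design effect and below 50% without it

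*Protocol article*

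**What the plan says.** Section 2.4 of the protocol article sizes each survey for precision of a single prevalence that "does not exceed 30%, with an absolute precision of ± 5% and a confidence level of 95" per cent. It states that "A design effect of 1.5 has been applied" and allows for refusals. For the comparison over time it says: "A before-and-after analysis will be conducted with 600 independent participants at each time point". The stated capability for health-related quality of life (HRQoL) is "absolute changes of around 10%, with a confidence level of 95% and a statistical power close to 80" per cent. After conceding that stratification may lower power for social inequalities, the section concludes that "we estimate that the sample size will be sufficient to identify relevant trends and significant differences in social inequalities in the studied sample". No differential, group size or power accompanies that conclusion.

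Section 2.8 says how changes in inequality will be examined: additional models "including interaction terms of time with sex, age group and other sociodemographic variables to assess the changes in social inequalities in HRQoL". P below 0.05 is to serve "as a reference to identify statistically significant differences", with caution advised for smaller subgroups, and "The possibility of a type II error (false acceptance of the null hypothesis) will be considered".

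**The concern.** A change in inequality over time is a difference of differences: the before–after change in one group minus that in another. It is estimated much less precisely than the overall before–after change. A sample with about 80% power for an overall 10-point change therefore cannot have similar power for a 10-point difference in change between groups. Section 2.4 gives the overall benchmark and then extends sufficiency to inequalities without a separate calculation.

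Health equity is part of the stated study aim. If readers accept the sufficiency sentence, a non-significant interaction may be read as evidence that inequalities did not move, when the surveys could have missed a substantial shift. At low power, an interaction that does reach significance is also at risk of overstating the true differential.

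**Working it through.** **Inputs from the article.** 600 independent participants per wave, design effect 1.5, prevalence up to 30%, benchmark change 10 points and power close to 80% (section 2.4); migrant quota 25.6%, about 154 of 600 (section 2.3). Section 2.8 dichotomises HRQoL at the whole-sample median if it is not normal, which puts prevalence near 50%. The range 30–50% covers both cases.

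**Assumptions.** Two-sided 0.05 (sidedness is not stated); 50:50 sex split (the quota table is not shown); equal prevalence in the four cells; no gain from covariate adjustment; the 10% benchmark read as percentage points of a binary indicator.

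**Step 1: reproduce the plan's own figures.**
- Precision: 1.96² × 0.3 × 0.7 / 0.05² = 322.7; × 1.5 = 484. Allowing for 20% refusal gives 605 (484/0.8) or 581 (484 × 1.2). Both are within 3% of the stated 590.
- Overall change: effective n per wave = 600/1.5 = 400. Power = Φ((0.10 − 1.96·SE₀)/SE₁), with SE₀ = √(2p̄(1−p̄)/400) and SE₁ = √((p₁(1−p₁)+p₂(1−p₂))/400). For 50% to 40%: SE₀ = 0.0352, SE₁ = 0.0350, power 81%. For 30% to 40%: 84%. For 30% to 20%: 91%.
- Without the design effect the same three cases give 94–98%. The stated figure is therefore matched with the design effect, which makes that the consistent basis for the interactions. Both bases are shown below.

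**Step 2: standard error of the interaction.** With effective n per wave nₑ and group share s:

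SE = √{2p(1−p) × [1/(nₑs) + 1/(nₑ(1−s))]}

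For s = 0.5 this is exactly twice the SE of the overall change, √(2p(1−p)/nₑ). For s = 0.256 it is 2.29 times.

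**Step 3: power for a 10-point differential change and the differential detectable with 80% power.** Power = Φ(0.10/SE − 1.96) + Φ(−0.10/SE − 1.96); detectable size = 2.80 × SE.

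Example (sex, p = 0.30, nₑ = 400): SE = √(0.42 × (1/200 + 1/200)) = 0.0648. Then 0.10/0.0648 = 1.543 and Φ(−0.417) ≈ 0.34. Detectable size 2.80 × 0.0648 ≈ 18 points.

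| Interaction | Design effect | p | SE | Power, 10 points | Detectable at 80% |
|---|---|---|---|---|---|
| Time × sex | 1.5 | 0.30 | 0.0648 | 34% | 18 points |
| Time × sex | 1.5 | 0.50 | 0.0707 | 29% | 20 points |
| Time × migrant | 1.5 | 0.30 | 0.0742 | 27% | 21 points |
| Time × migrant | 1.5 | 0.50 | 0.0810 | 23% | 23 points |
| Time × sex | 1 | 0.30 | 0.0529 | 47% | 15 points |
| Time × sex | 1 | 0.50 | 0.0577 | 41% | 16 points |
| Time × migrant | 1 | 0.30 | 0.0606 | 38% | 17 points |
| Time × migrant | 1 | 0.50 | 0.0661 | 33% | 19 points |

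Letting prevalence differ between the four cells does not change the picture. Over the patterns tried, with prevalences from 20% to 50%, the highest power was about 52% (sex, no design effect).

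**Step 4: continuous score.** In SD units, replace p(1−p) by 1. For sex with design effect 1.5, SE = √(2 × (1/200 + 1/200)) = 0.141, so the detectable interaction is 0.40 SD; for migrants it is 0.45 SD. Without the design effect they are 0.32 and 0.37 SD.

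**Step 5: cross-sectional gaps, for contrast.** Power for a 10-point gap between groups (30% against 20% or 40%, over both groups and both design effects) is 44–81% in one wave and 73–98% with both waves pooled.

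**The case against.** The sentence in section 2.4 is hedged: it concedes lower power, names no effect size and covers trends as well as significant differences. It also does not speak only of changes over time. The article plans stratified means and models of sociodemographic associations, and for gaps of that kind the sample is considerably better. This stands. A reader might infer that the sentence is simply false, but the article does not support that. The sentence is unsupported for one of the things it covers, and differentials of about 15–23 points would be detectable.

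The design effect is set for a single prevalence. Sex is a stratifier within census sections, so section effects may partly cancel in a time-by-sex contrast, and 1.5 may be too severe. This also stands, which is why both bases are given. Power for a 10-point differential is inadequate on either.

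Section 2.8 uses linear models first and dichotomises only if the scores are not normal. The article gives no benchmark on the score scale, so a percentage-point shortfall cannot be carried over; only the detectable size of 0.32–0.45 SD can be stated. Covariate adjustment might improve it somewhat.

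Two further inferences should not be drawn. One is that power falls to 20%: that needs about 480 usable responses per wave, whereas the article states 600 participants at each time point. The other is that an open list of interactions will yield mostly chance findings. Section 2.8 specifies the interactions for HRQoL, which has two summary scores. The exact factor list and any multiplicity rule may properly sit in an analysis plan that is not shown. Their absence is no finding.

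**Conclusion.** The concern holds for changes in inequality over time and not beyond that. At the article's own 10-point benchmark, and on the basis that reproduces its stated power, the planned interactions would miss a true differential about two times in three for sex and about three in four for migrant status. Dropping the design effect leaves a better-than-even chance of missing it in every case tabulated. The section 2.8 caution about type II error points the right way, but it does not reconcile with a sample-size section that declares the sample sufficient.

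The exact figures rest on the assumptions listed with the check. The conclusion depends little on them, because the at-least-twofold ratio of standard errors holds whatever the prevalence or design effect, provided both are common to the groups.

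**What to change.** In section 2.4, limit the sufficiency sentence to cross-sectional differences between groups. Add the detectable differential changes at 80% power: about 18–20 points for sex and 21–23 points for migrant status with the design effect, 15–19 points without it, and 0.32–0.45 SD on the continuous score, with their assumptions.

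In section 2.8, label the time-by-group analyses exploratory. Carry the absolute and relative reporting already planned through to differences in change, each with a 95% confidence interval. State that neither significance nor non-significance of an interaction will be read as evidence on changes in inequality.

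The cost is a less favourable stated capability; no extra participants are needed. Powering for a 10-point differential instead would take 600 × (detectable size/10)² per wave: about 1,320–2,355 for sex and 1,730–3,090 for migrant status, using the unrounded detectable sizes.

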### Documentation and classification of co-creation cycles

2.5

The development of new initiatives is expected to follow a cyclical process, in which community stakeholders collaboratively identify priorities, co-design and implement actions, and iteratively evaluate and adapt them, informed by the RE-AIM framework (Reach, Effectiveness, Adoption, Implementation, and Maintenance). To document each cycle, a standardized matrix will be used to record key characteristics, including a brief description of the activities developed, target population, setting, intensity and duration, level of community involvement, and evaluation results (quantitative and qualitative). In line with the project's Data Management Plan, structured outputs from each cycle—including short reports and infographics summarizing key outcomes, agreements, and process evaluation findings—will be made available through the project's open-access repository (i.e., Zenodo). This approach will enable cycles to be grouped into analytically meaningful categories while preserving relevant contextual detail.

### Procedure

2.6

For each sampling route, a random point within the census section will be selected to determine the starting location for data collection. From there, a random sample of households will be chosen along the route, and finally, one individual per household will be recruited according to the quota strategy (Supplementary Table S1).

A team of four trained interviewers will conduct face-to-face the data collection in the sampled households or, when appropriate, in workplaces, as explained below. Using tablet devices, they will first provide participants a detailed explanation of the purpose of the study, the confidentiality of their responses, and their right to withdraw at any time without consequences. Written informed consent will then be obtained from all participants.

Surveys may be conducted in workplaces or other communal spaces in the community when an imbalance in the sample—particularly an under-representation of the working-age population—has been identified following household-based recruitment efforts. In this case, participation will be offered only to individuals whose residence in the study area has been previously verified.

In addition, we will have the support of the intercultural mediators, previously trained in public health by the Elche Public Health Center to address possible linguistic or cultural barriers to participation for the Arabic-speaking population. If people with communication difficulties are identified, a specific day will be organized to deal exclusively with these cases, with the assistance of one or more intercultural mediators who will assist the team of interviewers in person or by phone. These mediators will receive specific training in the administration of the questionnaire, the use of the electronic devices and compliance with the study's ethical protocol. This approach ensures the inclusion and participation of all segments of the population, including hard-to-reach persons.

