### Study population

2.3

We will recruit 600 participants using a stratified random sampling based on the 2021 census sections. The sampling will be stratified by census section, sex, age group to ensure its representativeness using population quotas from census data provided by Spain's National Statistics Institute (INE, Supplementary Table S1)(10). Furthermore we will apply an overall migrant quota of 25.6%. By using a stratified sampling, we ensure a representative sample of the neighbourhood's population, also in terms of representativeness of men and women across age groups for each of the different census sections that compound the District 2 of Elche. Furthermore, given that representativeness is a challenge for any population survey, targeted outreach through social media, local traditional media and community-based engagement activities will be employed to increase community awareness and improve response rates.

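### The survey is labelled a stratified random sample, but the field procedure is a random-route quota sample, and the 20% rejection allowance is applied to the wrong number

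*Protocol article*

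**What the plan says.** **Sampling claim.** The abstract (Methods) and section 2.3 (Study population) both name the design as stratified random sampling: "We will recruit 600 participants using a stratified random sampling based on the 2021 census sections". Section 2.3 says that this ensures a representative sample of the neighbourhood. The same section fills the strata (census section, sex, age group) with population quotas and adds an overall migrant quota of 25.6%.

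**Field procedure.** Section 2.6 starts each route at a random point in the census section and takes a random sample of households along it. Then "one individual per household will be recruited according to the quota strategy". If the sample proves unbalanced after household recruitment, interviews may also be held in workplaces or other communal spaces, with residence verified. Section 2.8 (Data analysis) states that no survey weights will be used.

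**Sample size.** Section 2.4 assumes that the prevalence of the variables of interest "does not exceed 30%, with an absolute precision of ± 5% and a confidence level of 95" per cent. It adds: "A design effect of 1.5 has been applied". Finally, "a rejection rate of up to 20% has been considered, implying the need to recruit at least 590 participants". For the comparison over time: "A before-and-after analysis will be conducted with 600 independent participants at each time point".

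**The concern.** A stratified random sample gives each member of a stratum a known chance of selection. Confidence intervals and the claim to represent the district rest on that. Under section 2.6 the last stage is a quota, and part of the sample may come from outside the household frame. Within a cell, who is interviewed then depends partly on who is reachable and willing. Filled quotas look the same whatever the refusal rate.

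This matters more here than in a single descriptive survey. The main inference compares two independent samples, before and after three years of community engagement, without a control area. Willingness to take part could plausibly change between waves: section 2.2 expects the Basic Health Councils to mobilise participation, and section 2.3 plans outreach to raise response. Willingness is also close to what some of the scales measure, such as social capital and community belonging. A shift in who agrees could be read as an effect.

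The rejection allowance adds a second ambiguity. Refusal raises the number of people to approach. Section 2.4 uses it to raise the number to recruit and then analyses everyone recruited, so the reader cannot tell whether 600 counts approaches or completed interviews.

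**Working it through.** **1. Sampling, claim against procedure**

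| Stage | Claim (abstract, 2.3) | Procedure (2.6, 2.8) |
|---|---|---|
| Start point and household | random | random start point, random households on a route |
| Person | random within stratum | by quota; no random choice within the household is described |
| Shortfall | not mentioned | workplaces or communal spaces |
| Weights | not mentioned | none |

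The first row agrees. The person stage and the top-up break the chain of known probabilities, and nothing in the stated analysis restores it. The design effect of 1.5 widens an interval; it does not correct for who is chosen inside a cell.

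**2. Reproducing 590**

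Inputs from section 2.4: p = 0.30, d = 0.05, z = 1.96, design effect 1.5, rejection 20%.

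- n0 = 1.96² × 0.30 × 0.70 / 0.05² = 322.7
- With the design effect: 322.7 × 1.5 = 484.0 completed interviews
- Allowance by division: 484.02 / 0.80 = 605.03, or 606 rounded up
- Allowance by multiplication: 484.02 × 1.2 = 580.8, or 581

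The stated 590 lies between the two conventions and within 3% (17.7) of each. It corresponds to an inflation of 590 / 484.02 = 1.219, that is 18.0% rejection.

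A finite-population correction also comes close. The document gives 36,065 residents of all ages but no adult count. With an assumed adult population N of 20,000 to 30,000, 484.02 / (1 + 483.02 / N) gives 472.6 to 476.4. Divided by 0.80 and rounded up, that is 591 to 596.

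**3. What 600 delivers under each reading**

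Half-width = 1.96 × √(1.5 × 0.21 / n):

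- 600 completed interviews: ±4.49 points, better than the ±5 target
- 600 approached and 20% refusing: 600 × 0.80 = 480 interviews, ±5.02 points, essentially the target

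**4. Differential refusal, illustration only**

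The document gives neither per-wave refusal rates nor how refusers differ from participants. Assume that refusers differ by 10 points in the prevalence of poor health-related quality of life, and that this gap is the same at both waves. The spurious before-after change is then the difference in refusal rate × 10 points:

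- 20% against 25%: 0.05 × 10 = 0.5 points
- 20% against 35%: 0.15 × 10 = 1.5 points

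The 35% is above the rate of up to 20% that the plan allows for.

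**The case against.** The strongest reply is that the article hides little. Section 2.3 mentions quotas in the sentence that describes the stratification. Section 2.4 fixes the same sampling design at both waves. Section 2.6 limits the top-up to an imbalance found after household recruitment, and adds mediators. Section 2.8 adjusts for education, ethnicity, migration status, income and employment. The Discussion asks for caution, reads the results as time trends, and names migrant under-representation with its direction of bias.

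Much of this stands, and it rules out four stronger readings that a reader might infer:

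- *That refusers are replaced within quotas.* The document never says so. Filling quotas to a fixed 600 suggests it, but the rule may sit in a fuller protocol or field manual, and its absence from an article is not the finding.
- *That 590 does not follow from the inputs.* The usual formulas give 581 to 606, which brackets it. Only the exact rounding is unexplained.
- *That the sample is too small.* Precision is met with 600 completed interviews and practically met with 480.
- *That the bias is 1.5 points.* That figure rests on assumed inputs, is small beside the change of around 10% for which section 2.4 claims power, and would arise equally in a true random sample with the same non-response.

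The reply does not rescue the label. Mentioning quotas does not make a quota sample random. The same design at both waves does not guarantee the same willingness to take part. Covariate adjustment covers only what is measured. The limitations name neither quota selection nor differential refusal.

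**Conclusion.** The point holds as a wrong description of the design, and it is worth correcting. The procedure in section 2.6 is a random-route quota sample. Its balance is assured only for census section, sex, age group and overall migrant share, so the claim of a representative stratified random sample goes further than the design supports. This conclusion does not depend on how refusals are handled.

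The 20% allowance is attached to the wrong quantity. If 600 are completed interviews, which is the natural reading of sections 2.3 and 2.4, the allowance is redundant: about 484 suffice at 30% prevalence and a design effect of 1.5. No precision is lost.

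The practical consequence is for interpretation. A change in who agrees to take part between baseline and 2029 could pass for a change in the district. Its size cannot be derived from the document.

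**What to change.** 1. **Abstract, sections 2.3 and 2.6:** call the design random-route quota sampling and limit the representativeness claim to the quota variables. State how refusals and non-contacts are handled.
2. **Section 2.4:** state that 600 means completed interviews and that the 20% allowance concerns people approached (about 606 approached for 484 completed interviews). Give ±4.5 points as the precision at 600.
3. **Fieldwork and reporting:** record contact outcomes (interview, refusal, nobody home, nobody eligible for the open cell, language barrier) by census section on the tablets for the 2029 wave. Baseline recruitment began on 22 October 2025, so for that wave recover whatever contact records exist. Report the refusal rate per wave beside the before-after estimate.
4. **Discussion:** name quota selection and differential refusal as limitations.

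The cost is wording and a short form on devices already in use, with no extra participants. The sampling claim becomes less favourable, and baseline refusal may be only partly recoverable.
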